## Abstract

**Background:**

Maternal depression can be harmful to both mothers and their children. Omega-3 polyunsaturated fatty acid (PUFA) supplementation has been investigated as an alternative intervention for pregnant women with depressive symptoms because of the supporting evidence from clinical trials in major depression, the safety advantage, and its anti-inflammatory and neuroplasticity effects. This study examines the efficacy of omega-3 PUFA supplementation for pregnant women with depressive symptoms in Taiwan and Japan, to provide evidence available for Asia. The rationale and protocol of this trial are reported here.

**Methods:**

The Synchronized Trial on Expectant Mothers with Depressive Symptoms by Omega-3 PUFAs (SYNCHRO) is a multicenter, double-blind, parallel group, randomized controlled trial. Participants will be randomized to either the omega-3 PUFAs arm (1,200 mg eicosapentaenoic acid and 600 mg docosahexaenoic acid daily) or placebo arm. Primary outcome is total score on the Hamilton Rating Scale for Depression (HAMD) at 12 weeks after the start of the intervention. We will randomize 56 participants to have 90 % power to detect a 4.7-point difference in mean HAMD scores with omega-3 PUFAs compared with placebo. Because seafood consumption varies across countries and this may have a major effect on the efficacy of omega-3 PUFA supplementation, 56 participants will be recruited at each site in Taiwan and Japan, for a total number of 112 participants. Secondary outcomes include depressive symptoms at 1 month after childbirth, diagnosis of major depressive disorder, changes in omega-3 PUFAs concentrations and levels of biomarkers at baseline and at 12 weeks’ follow-up, and standard obstetric outcomes. Data analyses will be by intention to treat. The trial was started in June 2014 and is scheduled to end in February 2018.

**Discussion:**

The trial is expected to provide evidence that can contribute to promoting mental health among mothers and children in Asian populations.

**Trial registration:**

Clinicaltrials.gov: NCT02166424. Registered 15 June 2014; University Hospital Medical Information Network (UMIN) Center: UMIN000017979. Registered 20 May 2015.

**Electronic supplementary material:**

The online version of this article (doi:10.1186/s12888-016-1031-2) contains supplementary material, which is available to authorized users.

## Background

A systematic review reported the prevalence of depression during pregnancy was 7.4 % for the first trimester, 12.8 % for the second, and 12.0 % for the third [1]. A meta-analysis estimated the prevalence of major and minor depression in the range of 6.5 to 12.9 % during the different trimesters of pregnancy and during the first 12 months postpartum [2]. Depression during pregnancy can have harmful effects on both the mother and child. The mother may experience difficulties performing daily activities, fail to seek prenatal care, have a poor diet, use tobacco, alcohol, or other harmful substances, and be at risk of self-harm or suicide [3]; fetal growth rate may be slower; and the child may have temperament or behavioral problems later [4–6].

The established treatment options for depression include antidepressants, cognitive behavioral therapy (CBT), and interpersonal psychotherapy (IPT). However, there are some limitations to each of these options. In terms of antidepressants, guidelines recommend all antidepressant drugs be used with caution during pregnancy and that selective serotonin reuptake inhibitors such as paroxetine be avoided [7, 8]. In fact, it was found in a population screening study of pregnant women attending antenatal clinics that only 11 % of pregnant women with major depressive disorders (MDD) were actually receiving suitable antidepressant medication [9]. Both CBT and IPT are recommended for pregnant women with mild or moderate depression [10] and an RCT has shown that IPT was effective for depression during pregnancy [11], but pregnant women cannot always access CBT or IPT. Identifying a safe alternative treatment strategy for depression during pregnancy is therefore desirable.

Many meta-analyses of RCTs [12–19], although not all [20, 21], support the positive effects of omega-3 polyunsaturated fatty acid (omega-3 PUFA) supplementation on depressive symptoms. The latest evidence supports the efficacy of omega-3 PUFAs rich in eicosapentaenoic acid (EPA) against depression [14, 16–18].

Omega-3 PUFAs are essential nutrients for maintaining physiological function of the mothers and infants during pregnancy. A previous study showed that omega-3 PUFA content in the brain of pregnant rats can be reduced after a single reproductive cycle when they are deprived of sufficient dietary omega-3 PUFAs, a reduction which may affect neuronal function [22]. In addition, another study reported that the brain decreases in volume in pregnant women [23]. It has been suggested that changes in the phospholipid content of the brain’s membranes could reduce brain size [24]. It is known that the composition of maternal phospholipid membranes can be altered during pregnancy by the fetus scavenging essential fatty acids such as omega-3 PUFAs, and this could potentially change brain morphology [23]. A lack of omega-3 PUFAs, then, may have a harmful effect on maternal mental health as well as on neurodevelopment of the fetus and infant. A naturalistic longitudinal study showed that lower seafood intake in pregnant women was associated with an increased risk of their children having suboptimum neurodevelopment [25]. To date, although two RCTs have failed to show the efficacy of omega-3 PUFAs for pregnant women with depression [26, 27], the supplements used contained high levels of docosahexaenoic acid (DHA) rather than EPA.

In a previous RCT conducted in Taiwan, our group showed the efficacy of supplements with a high ratio of EPA (2.2 g daily) to DHA (1.2 g daily) for depression in pregnancy [28]. However, it is not yet clear what the appropriate amount of supplemental omega-3 PUFAs is and it may differ between countries because of national differences in the consumption of fish, which is a rich source of omega-3 PUFAs. Although fish consumption in Taiwan is higher than in most Western countries, it is half that in Japan [29]. The recommended daily intake for pregnant women in Japan is 1.8 g of omega-3 PUFAs [30], and the usual dose of pure EPA as a prescription drug is also set at 1.8 g daily.

Recently, we suggested the potential efficacy of moderate amount of omega-3 PUFAs supplementation for improving depressive symptoms in our open label trial conducted in Japan and Taiwan [31]. The objective of the present randomized controlled trial is to determine the efficacy of a daily dose of 1.8 g of omega-3 PUFAs supplements (1.2 g EPA and 0.6 g DHA) for depressive symptoms in pregnant women in Japan and Taiwan. Examining the efficacy and safety of 1.8 g of omega-3 PUFAs supplementation in different countries is clinically relevant because not only is fish consumption generally higher and the prevalence of depression generally lower in East Asian countries such as Japan and Taiwan compared with Western countries, but also there are considerable differences between East Asian countries [29]. The study is called the Synchronized Trial on Expectant Mothers with Depressive Symptoms by Omega-3 PUFAs (SYNCHRO), and this paper explains the rationale and describes protocol of the trial. An additional file provides the completed SPIRIT 2013 Checklist (see Additional file 1).

## Methods/Design

SYNCHRO is a multicenter, double-blind, parallel group, randomized controlled trial that will allocate participants to an intervention arm to receive omega-3 fatty acid supplementation or a parallel placebo arm in the ratio of 1:1. The trial will run from June 2014 through February 2018, with participant enrollment between June 2014 and August 2017.

The study was registered at clinicaltrials.gov (NCT02166424) on June 15, 2014 and the University Hospital Medical Information Network (UMIN) Center (UMIN000017979) on June 22, 2015.

### Inclusion criteria

Pregnant women who are between 12 and 24 weeks of gestation will be recruited and followed through their pregnancy and up to 4 weeks after childbirth. The inclusion criteria are:Pregnant and aged ≥20 yearsJapanese conversational ability at the Japan site or Chinese conversational ability at the Taiwan site to ensure participants have sufficient understanding of the trial’s scope and can provide written informed consentPlanning to remain in the Tokyo area or Taichung area for 4–6 weeks after childbirthEdinburgh Postnatal Depression Scale (EPDS) score of ≥9In good physical health as judged by an obstetrician

### Exclusion criteria

The presence of any of the following will result in exclusion from the trial.History or current suspicion of psychosis, bipolar I disorder, substance abuse or related disorder, eating disorder, or personality disorderSerious psychiatric symptoms, such as self-harm behavior, or in need of rapid psychiatric treatmentNormal birth not expected (e.g., fetal malformation)History of bleeding disorder such as von Willebrand’s DiseaseRegular treatment with aspirin or warfarin for the past 3 monthsSmoking habit of ≥40 cigarettes per dayRegular treatment with ethyl icosapentate or regular consumption of omega-3 PUFA supplements for the past 3 monthsHabit of eating fish as a main dish ≥4 times per week

### Procedure

Eligible patients will be screened using the EPDS at three locations in cooperation with obstetricians: Toda Chuo Women’s Hospital and the National Center for Child Health and Development, both in Japan, and China Medical University Hospital, Taiwan. Toda Chuo Women’s Hospital is a local base hospital, and the National Center for Child Health and Development and China Medical University Hospital are academic hospitals. Clinical research coordinators, who will be well-trained nurses, psychologists or psychiatrists, will invite eligible patients to take part in the study. Patients will receive a comprehensive obstetric examination before the study commences and undergo a baseline assessment before randomization. Figure 1 shows a flow diagram of the study protocol.

**Fig. 1 Fig1:**
[figure not shown]
Flow diagram of the study. EPDS: Edinburgh Postnatal Depression Scale; MDD: major depressive disorders

### Randomization

Central registration involved assigning participants to each group according to an assignment diagram that was developed by a statistician. Using a computer-generated random allocation sequence, they created block randomization tables with two stratification factors: diagnosis of current MDD and study site. The test will be double-blinded and only after all participants have completed the protocol and all the results have been tabulated will the research term be informed of the results of the randomization. Stratification was justified by previous studies: the results of a meta-analysis showed some evidence supporting the benefits of omega-3 PUFAs in individuals diagnosed with MDD but no evidence supporting any benefits in individuals without MDD [32]. Moreover, a previous study showed that seafood consumption predicted prevalence rates of postpartum depression across countries [33].

### Intervention

Participants will take omega-3 PUFAs capsules or placebo capsules for 12 weeks, and can take an entire day’s dosage at once or spread throughout the day. The omega-3 PUFAs capsules have been formulated to each contain 134 mg of EPA and 67.7 mg of DHA, and a total of 9 capsules containing a total of 1206 mg EPA and 609 mg DHA will be administered daily. The placebo capsules have been formulated to contain 320 mg of olive oil and 9.9 mg of omega-3 fatty acids. Trace amounts of semi-deodorized fish oil are added to the control oil so that its smell is not perceivably different from that of the active oil.

Adherence to the regimens will be checked by clinical research coordinators. Whole blood samples (7 ml) collected with ethylene-diamine tetraacetic acid will be taken at baseline, at 12 weeks’ follow-up, and at 1 month after childbirth and omega-3 PUFAs will be determined as described previously [34]. Briefly, erythrocytes will be washed two time with saline and stored at−80 °C until analysis. The method of Bligh and Dyer [35] will be used to extract total lipids, and total phospholipid fractions will be separated by thin-layer chromatography and transmethylated with by treatment with a mixture of HCl and methanol. Next, fatty acid composition will be analyzed by gas chromatography (GC-2014 Shimadzu Corporation, Kyoto, Japan) controlled with GC-solution version 2.3 (Shimadzu Corporation, Kyoto, Japan) and equipped with a DB-225 capillary column (length, 30 m; internal diameter, 0.25 mm; film 0.25 μm; J&M Scientific, Folsom, CA).

### Assessment

The assessment schedule from baseline to 1 month after childbirth is shown in Table 1.

**Table 1 Tab1:** Outcome measures and assessments

	Baseline	12 weeks	1 month after childbirth
Primary outcome			
HAMD	+	+	+
Secondary outcome			
MINI	+	+	+
EPDS	+	+	+
BDI-II	+	+	+
Plasma	+	+	+
Serum	+	+	+
Other measures			
Demographics	+		
Obstetric outcomes			+
Erythrocyte	+	+	+
Adverse effects		+	+

*HAMD* hamilton rating scale for depression (HAMD), *MINI* mini international neuropsychiatric interview, *EPDS* Edinburgh postnatal depression scale, *BDI*-II beck depression inventory-II

### Outcome measures

#### Primary outcome

The primary outcome is total score on the 17-item Hamilton Rating Scale for Depression (HAMD) [36, 37] at 12 weeks after the start of the intervention. HAMD is a widely used structural interview for assessment of depressive symptoms and has been used during pregnancy and in the postpartum period [26, 28, 38]. Trained psychiatrists, psychologists, or nurses will conduct the structured interviews for the evaluation. To assess inter-rater reliability, 3 well-trained raters in Japan and 2 well-trained raters in Taiwan have independently assessed the same person acting as a patient in a video. The original video was made in Japanese and then translated into Chinese for the raters in Taiwan. The maximum variance in scores among the 5 raters from the expert gold standard score was satisfactory for all the HAMD items. The intraclass correlation coefficient for the total HAMD score among the 5 raters was 0.967 (95 % confidence interval, 0.934–0.986).

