### Estimation of sample size

The expected difference in total HAMD score between the two arms at 12 weeks’ follow-up is set at 4.7 according to a previous study [28]. It is expected that 12 % of participants will discontinue the test capsules or drop out of the trial. Given an α level of 0.05 (two-tailed), a β level of 0.10, and standard deviation of 5, the desired number of participants will be 28 in each arm and 56 in total. Because a previous study suggested that seafood consumption varied across countries [33] and this may have a major effect on the efficacy of omega-3 PUFAs, 56 participants will be recruited at each site in Japan and Taiwan. Thus, the total number of participants will be 112. However, it is possible that enrollment will be halted before reaching this target if significant financial or logistical factors arise, or that number of cases at one of the sites may exceed the target number depending on the accumulation of cases at the other site.

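### The inter-rater ICC of 0.967 cannot be for the HAMD total score, because only one acted patient is described; it is most likely agreement across the 17 items of one interview

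*Protocol article*

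**What the plan says.** The Primary outcome section of the Protocol article makes the total score the endpoint: "The primary outcome is total score on the 17-item Hamilton Rating Scale for Depression (HAMD"), assessed at 12 weeks. It then describes a rater exercise that is already complete. The raters were "3 well-trained raters in Japan and 2 well-trained raters in Taiwan", who "have independently assessed the same person acting as a patient in a video". On the language versions it says: "The original video was made in Japanese and then translated into Chinese for the raters in Taiwan". No second patient or video is mentioned.

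Two results are given. One is about items and carries no figures: "The maximum variance in scores among the 5 raters from the expert gold standard score was satisfactory for all the HAMD items". The other is numerical and is labelled as the total: "The intraclass correlation coefficient for the total HAMD score among the 5 raters was 0.967", with a 95 % confidence interval of 0.934 to 0.986.

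**The concern.** The described design and the label on the result do not fit together. An ICC for a total score is the share of total variance that lies between patients. Five raters scoring one patient produce five totals and no between-patient variance, so neither an estimate nor an interval can be formed.

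The figure is the only number offered on the measurement quality of the primary outcome. If it is really agreement across items of one interview, it is high largely because some items score high and others near zero. It then says little about whether raters, or the two language groups of raters, arrive at similar totals. A reader would take 0.967 as evidence that the endpoint is measured almost without rater error, and the exercise described cannot show that.

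**Working it through.** **Inputs**, all from the Primary outcome section: raters k = 5 (3 + 2); patients rated = 1; items in the scale = 17; stated ICC r = 0.967; stated 95 % limits 0.934 and 0.986. The ICC form is not stated, so several were tried.

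**Step 1: the figure as labelled.** With n targets the between-target degrees of freedom are n − 1. For one patient this is 0, so the ICC and its interval are undefined.

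**Step 2: which n gives the stated interval?** The usual F-based limits apply. For the one-way, average-of-raters form:

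- F = 1/(1 − r) = 1/0.033 = 30.30
- lower limit = 1 − F₁/F, with F₁ the 97.5 % point of F on (n − 1, n(k − 1)) degrees of freedom
- upper limit = 1 − 1/(F × F₂), with F₂ the 97.5 % point on the degrees of freedom reversed

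With n = 17 the degrees of freedom are 16 and 68, F₁ = 2.005 and F₂ = 2.432. The lower limit is 1 − 2.005/30.30 = 0.9338 and the upper limit is 1 − 1/(30.30 × 2.432) = 0.9864. Rounded, this is 0.934 to 0.986, the stated interval.

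For the single-rater form, F = (1 + 4 × 0.967)/0.033 = 147.5, and the limits at n = 17 are 0.9355 to 0.9862 (one-way) or 0.9351 to 0.9863 (two-way consistency).

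**Step 3: other values of n** (two-way consistency, r = 0.967, k = 5):

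| Targets n | Single rater | Average of raters |
|---|---|---|
| 1 | undefined | undefined |
| 5 | 0.885–0.996 | 0.877–0.996 |
| 10 | 0.921–0.990 | 0.918–0.991 |
| 16 | 0.934–0.987 | 0.932–0.987 |
| 17 | 0.935–0.986 | 0.933–0.986 |
| 18 | 0.936–0.986 | 0.935–0.986 |
| 20 | 0.938–0.985 | 0.937–0.985 |
| 30 | 0.945–0.982 | 0.944–0.983 |

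The stated interval points to about 17 targets. It does not single out 17: if 0.967 is a rounded 0.9665, the one-way average form with n = 18 gives 0.9341 to 0.9858, which also rounds to 0.934 to 0.986.

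**Step 4: can an across-item ICC be high while totals differ?** An invented example: rater 1 scores 17 items (in arbitrary order) 3, 2, 1, 2, 1, 2, 3, 1, 0, 2, 1, 1, 1, 0, 0, 2, 0. Raters 2 to 5 copy this but add one point on item 3; on items 5 and 10; on items 2, 5, 7 and 11; and on items 4, 6, 8, 12 and 13. The totals are 22, 23, 24, 26 and 27. The mean squares are 5.231 (items), 0.253 (raters) and 0.128 (residual).

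- Average of raters, consistency: 1 − 0.128/5.231 = 0.976 (absolute agreement 0.974)
- Single rater, consistency: (5.231 − 0.128)/(5.231 + 4 × 0.128) = 0.889 (absolute agreement 0.883)

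In the average-of-raters form, an across-item ICC above 0.967 therefore coexists with a 5-point spread of totals, against a target difference of 4.7 points. In the single-rater form the same ratings fall well below 0.967.

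**Step 5: the sample size.** The Estimation of sample size section gives a difference of 4.7, SD 5, two-sided α 0.05, β 0.10 and 12 % loss. Then 2 × (1.960 + 1.282)² × 25/4.7² = 23.8, so 24 per arm, and 24/0.88 = 27.3, so 28 per arm, as stated. The ICC does not enter.

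**The case against.** The strongest reply is that this is a label on a finished training exercise. It feeds no endpoint definition, test or sample size; the SD of 5 is set separately. A condensed article may also leave individual raters' totals to a fuller document. All of that stands, and it limits the weight of the point. It does not rescue the sentence, which states a figure that its own described design cannot produce.

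Four stronger readings are tempting, and the documents do not support them.

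- **That the 17-item origin is proven.** It is inferred from the width of the interval. The form and the ratings are not shown, 18 targets also fit within rounding, and about 17 separate cases may have been rated without the article saying so. In that event the description of one acted patient would be what needs correcting.
- **That the figure is used to declare the two countries' totals equivalent.** The article makes no such claim and plans no comparison of raw HAMD levels between countries. It stratifies randomization by site and estimates a difference between arms. Nor is the ICC the only reliability evidence: the item-level check against an expert standard bears on systematic shift, although no figures are given.
- **That an across-item ICC of 0.967 says nothing about totals.** This depends on the form. A consistency ICC ignores constant rater shifts and an absolute-agreement ICC penalises them. A single-rater value of 0.967 would be more reassuring than an average-of-raters value, as Step 4 shows.
- **That the raters are unreliable, or the trial's comparison biased.** The evidence of total-score reliability is absent; nothing shows that reliability is poor. Under double-blind, site-stratified allocation, a constant country or language shift falls about equally on both arms.

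**Conclusion.** The point holds as an error of labelling. From one acted patient, a total-score ICC and its confidence interval do not exist, so 0.967 (0.934 to 0.986) is not what the article says it is. This conclusion rests only on the article's own description. The likely explanation, agreement of 5 raters across the 17 items of one interview, rests additionally on the F-based interval calculation and remains an inference.

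In either case the figure, as reported, does not establish the reliability of the primary outcome. The planned 28 per arm at each site and the validity of the randomized comparison are not affected. It is worth correcting because it concerns the primary outcome and the correction is cheap.

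**What to change.** 1. Relabel the figure as item-level agreement within one scripted interview, and state the ICC form (single or average, consistency or absolute agreement). If several cases were in fact rated, correct the description instead and give their number.
2. If it is item-level agreement, stop citing it as evidence that the total score is reliable.
3. From the ratings already made, report each of the five raters' totals, its deviation from the expert total, and the Japan–Taiwan difference.
4. Enter study site as a covariate in the primary ANCOVA. The Primary analysis section names no specific covariates; if the full plan already includes site, nothing changes. Site is a randomization stratum, and including it keeps a constant country or language shift from adding noise to the arm comparison. Differences between raters within a site would remain.

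The cost is a reworded sentence, a small table from existing data and one model term. The downside is a less favourable reliability statement. No new patients are needed and trial conduct does not change. A true total-score ICC would need several recorded patients spanning the severity range, scored by all raters at both sites; that would be a separate exercise.
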